### Sample size

An overall sample size of 300 patients was defined according feasibility.

However, according with the primary endpoint and the study design, the statistical power estimation was performed.

More specifically, we simulated the width from the lower limit of 95% confidence intervals for the Ratio Between Two Proportions.

The following parameters and assumptions were included into the equation:overall sample size of 300 patients;assumption of the balanced numbers (1:1) of physically frail sarcopenic [3 ≥ SPPB score ≤ 8] and healthy active elderly [SPPB score > 8] individuals;assumption of the unbalanced numbers (2:1) of individuals with and without sleep disorders at the baseline;expected rate of 9% of SPPB score < 9 at 12 months in healthy active elderly individuals [SPPB score > 8] without sleep disorders [118–123];expected rate of 27% of inability to complete a 400 m walk test in less than 15 min (without sitting, stopping for more than one minute, receiving help, or using a walker) in physically frail sarcopenic elderly individuals [3 ≥ SPPB score ≤ 8] without sleep disorders [18];an overall risk ratio of 1.55 at 12 months for individuals with sleep disorders versus the ones without sleep disorders (pooled expected rate 18%);an alpha error of 5%;

Thus, to reject the null hypothesis the lower limits of the ratio must not be lower than 1.11 (corresponding to a 20% of the lower limit of the differences).

Participants will be enrolled at the Frail elderly lab of the Geriatric Clinic Unit within the Interagency integrated activity department of continuity and multicomplexity of the University Hospital of Parma, by acquisition of informed consent and if, upon the geriatric multidimensional assessment, the eligibility criteria given in this study protocol will be met.

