### Statistical methods

Data will be summarized using mean ± standard deviation (SD) or, for non-normally skewed distributions, as median and interquartile range (IQR). Incidence (mild cognitive impairment and cognitive frailty; dementia; recognised pre-frailty conditions; malnutrition; polypharmacy; multimorbidity), prevalence (mild cognitive impairment and cognitive frailty; recognised pre-frailty conditions; malnutrition; polypharmacy; multimorbidity) and mortality among healthy active and physically frail sarcopenic elderly individuals with and without sleep disorders will be compared using chi-square test, adjusted for age and sex.

According to the sample size estimation, 95% CIs will be calculated with Clopper-Pearson method and tested with a test for two proportions. For interpretative purposes multivariable logistic regression will be implemented. Moreover, to evaluate the outcome in terms of continue variable, multivariable ordinal logistic regression model will be used to estimate the association between the sleep disorders and the single unit of decrease in physical and functional score (SPPB score).

Since there will be multiple measures (baseline, + 12 months, + 24 months), the Mixed Model for Repeated Measure (MMRM) will be adopted for the longitudinal analyses.

The analyses will be centralized and performed by the Clinical and Epidemiological Research Unit at University Hospital of Parma using R-Cran and STATA statistical softwares.

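### The primary effect is planned as a risk ratio, but the only adjusted model for it yields an odds ratio, about 1.85 where the risk ratio is 1.55; report a standardised risk ratio from the same model

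*Protocol article*

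**What the plan says.** In the protocol article, Sample size works on the ratio scale throughout. The authors write that "we simulated the width from the lower limit of 95% confidence intervals for the Ratio Between Two Proportions", assume "an overall risk ratio of 1.55 at 12 months for individuals with sleep disorders versus the ones without sleep disorders" with a pooled rate of 18%, and state that "to reject the null hypothesis the lower limits of the ratio must not be lower than 1.11". The unexposed inputs are an "expected rate of 9% of SPPB score < 9 at 12 months in healthy active elderly individuals" and an "expected rate of 27% of inability to complete a 400 m walk test in less than 15 min" in the physically frail sarcopenic group. The groups are taken as 1:1 for function and 2:1 for sleep disorders, with 300 participants in all.

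Statistical methods ties the primary analysis to that section: "95% CIs will be calculated with Clopper-Pearson method and tested with a test for two proportions". It then adds: "For interpretative purposes multivariable logistic regression will be implemented". No other adjusted model is named for the binary primary outcome. The age- and sex-adjusted chi-square covers mortality and the listed incidence and prevalence outcomes, the ordinal model covers SPPB decrements, and the MMRM covers the longitudinal analyses.

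The Discussion counts adjustment for confounders among the strengths of the design and lists covariate adjustment among its countermeasures to confounding.

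**The concern.** This is an observational cohort, so the adjusted estimate is the one readers will rely on, and the plan itself gives it the interpretative role. An odds ratio approximates a risk ratio only when the outcome is rare. Here the planned unexposed risk in the frail stratum is 27%, and the exposed risk would be about 42%.

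A crude risk ratio of 1.55 printed beside an adjusted odds ratio near 1.85 suggests that adjustment strengthened the association, even when there is no confounding at all. The reverse can also happen: the change of scale can hide real attenuation. In either case the adjusted result cannot be compared with the effect for which the study was planned.

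**Working it through.** **Inputs (Sample size).** Unexposed risks 9% (healthy active) and 27% (frail); risk ratio 1.55; 150 participants per functional stratum; 2:1 exposure, so 100 exposed and 50 unexposed in each stratum.

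**The plan's own figures.** Pooled unexposed risk: (9% + 27%)/2 = 18%, as stated. Threshold: 1 + 0.20 × (1.55 − 1) = 1.11, as stated.

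**Assumptions added here.** Risk ratio 1.55 within each stratum, no confounding, and adjustment for the functional stratum only. The article gives no exposed risks by stratum and no covariate list.

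**Odds ratios.** OR = p1(1 − p0) / [p0(1 − p1)], with p1 = 1.55 × p0.

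| Group | p0 | p1 | OR |
|---|---|---|---|
| Healthy active | 9.00% | 13.95% | (0.1395 × 0.91)/(0.09 × 0.8605) = 1.64 |
| Frail | 27.00% | 41.85% | (0.4185 × 0.73)/(0.27 × 0.5815) = 1.95 |
| Crude, pooled | 18.00% | 27.90% | (0.279 × 0.82)/(0.18 × 0.721) = 1.76 |

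**Adjusted for stratum.** A logistic model with exposure and stratum, fitted to the expected cell counts, gives log odds ratio 0.6148, so OR = exp(0.6148) = 1.85 (95% CI at expected counts 0.99 to 3.44). Two checks agree:

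- Mantel-Haenszel: (13.95 × 45.5/150 + 41.85 × 36.5/150) / (86.05 × 4.5/150 + 58.15 × 13.5/150) = 14.415/7.815 = 1.84.
- Simulation of 2,000 studies of 300 participants: median adjusted OR 1.86.

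The step from 1.55 to 1.76 is the change of scale. The step from 1.76 to 1.85 is non-collapsibility of the odds ratio.

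**Does the gap depend on a common risk ratio?** Suppose instead that one odds ratio holds in both strata and the pooled exposed risk is still 27.9%. An OR of 1.8355 gives exposed risks of 0.1652/1.0752 = 15.36% and 0.4956/1.2256 = 40.44%, with mean 27.90%. The odds ratio is then about 1.84, so the gap remains.

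**Other reading of 18%.** If 18% is the rate over all participants, p0 = 0.18/(1/3 + 1.55 × 2/3) = 13.17% and p1 = 20.41%. The crude OR is 1.69. With the stratum rates scaled down by the same factor, the adjusted OR is 1.74.

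**More covariates.** Adding an independent prognostic covariate with SD 1.0 on the log-odds scale, marginal risks unchanged, raises the stratum ORs from 1.64 to 1.73 and from 1.95 to 2.21. The risk ratio stays at 1.55.

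**Masking.** An adjusted OR of 1.55 applied to unexposed risks of 9% and 27% gives exposed risks 0.1395/1.0495 = 13.29% and 0.4185/1.1485 = 36.44%, mean 24.87%. The standardised risk ratio is 24.87/18 = 1.38. Attenuation from 1.55 to 1.38 would then look like no change.

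**The 1.11 limit on the odds scale.** At baseline risks of 9%, 18% and 27% it becomes OR 1.12, 1.14 and 1.16, so it has no single equivalent.

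**What standardisation returns.** The fitted log-odds (intercept −2.4046, exposure 0.6148, stratum 1.4462) give unexposed risks of 8.28% and 27.72% (mean 18.0%) and exposed risks of 14.31% and 41.49% (mean 27.9%). The ratio is 1.55. Because the strata are equally mixed in both exposure groups, the logistic fit reproduces the pooled risks whatever the pattern by stratum.

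**The case against.** The strongest reply is that nothing is wrong as written. The article never says that an odds ratio will be reported. It says only that the model will be fitted, and a standardised risk ratio is compatible with that. The covariate list and the details of reporting commonly sit in a statistical analysis plan, which is not shown. Logistic regression is a standard choice for a binary outcome, and a labelled odds ratio beside a labelled risk ratio need not mislead a careful reader. On the odds scale alone, stratum adjustment moves the figure only from 1.76 to 1.85, about 5%.

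Much of this stands, and it limits the point. Three stronger readings are tempting, and the document does not support them.

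- *That the primary inference is compromised.* The formal analysis is the unadjusted two-proportion test. Nothing applies the 1.11 rule to the logistic model.
- *That the logistic model is misspecified because the strata have different odds ratios.* Sample size gives an overall risk ratio and does not say that it holds within each stratum. If the odds ratio were constant instead, the logistic model would be right and a log-link model wrong. A log-link fit that returns 1.55 from data built with a common risk ratio proves nothing.
- *That 1.85 is what the study will report.* That figure rests on the assumptions listed in the working.

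What remains is that the article fixes the effect measure and, separately, a model whose direct output is on another scale, with no stated link between them.

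**Conclusion.** The point holds in a limited form, as a cheap improvement. The only adjusted estimate of the primary outcome would by default be an odds ratio, while the effect and its limit are planned as a risk ratio. Under the planning rates, with a common risk ratio of 1.55 and no confounding, the crude odds ratio is about 1.76 and the stratum-adjusted one about 1.85. The less natural reading of the 18% gives 1.69 and 1.74. The gap from 1.55 is present on every reading tried, and it does not need the common-risk-ratio assumption. The actual size will depend on the covariates chosen and the event rates observed.

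**What to change.** Keep the logistic model and add one sentence to Statistical methods: the adjusted result for the primary outcome will be reported as a marginal risk ratio, standardised over the covariate distribution of the cohort, with a delta-method or bootstrap 95% CI, and the odds ratio will be given as a supplement. Modified Poisson regression with robust variance is an acceptable alternative. Crude and adjusted results then share the planned scale, and any difference between them is no longer produced by the change of measure.

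The cost is slightly more analysis work. R and STATA, both already named, can do it, and no new data or visits are needed.

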**Fig. 7 Fig7:**
[figure not shown]
SOMNUS-DARE analytic aspects

It will be measured in terms of SPPB score < 9 [51, 52] for healthy active elderly individuals and in terms of inability to complete a 400 m walk test in less than 15 min (without sitting, stopping for more than one minute, receiving help, or using a walker) [53] for physically frail sarcopenic elderly Individuals.

The secondary and exploratory outcomes have already been listed in Table 1.

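### The supplementary ordinal model grades the outcome by SPPB decrease with no stratum limit, so in the frail stratum, where the outcome is 400 m walk failure, it does not grade the primary outcome

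*Protocol article*

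**What the plan says.** The Outcomes section of the protocol article defines physical and functional worsening at 12 months separately by stratum. For healthy active participants (baseline SPPB above 8) it is an SPPB score below 9. For physically frail sarcopenic participants it is "inability to complete a 400 m walk test in less than 15 min". The Sample size section plans on the same two definitions, with an "expected rate of 9% of SPPB score < 9 at 12 months in healthy active elderly individuals" and an "expected rate of 27% of inability to complete a 400 m walk test in less than 15 min", both for people without sleep disorders.

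The Statistical methods section first sets out confidence intervals and a test for two proportions, in line with the sample size estimation, then a multivariable logistic regression for interpretation. It adds that "to evaluate the outcome in terms of continue variable, multivariable ordinal logistic regression model will be used" to relate sleep disorders to the "single unit of decrease in physical and functional score (SPPB score"). SPPB is the only score named. No stratum is specified, and no graded form of the walk is described.

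**The concern.** The sentence introduces the ordinal model as another way of looking at the outcome, and it fixes the response variable. In the healthy active stratum the binary outcome and the graded response come from the same instrument. In the frail stratum they do not. A frail participant who goes from SPPB 6 to 5 and still completes the walk is worse in the ordinal model and a non-event in the primary analysis. One who stays at SPPB 5 and fails the walk is a primary event and unchanged in the ordinal model.

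What is at stake is interpretation. If the ordinal result is reported as the graded version of the primary result, agreement or disagreement between them will be given a meaning that it does not have in the frail stratum.

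A second, conditional issue concerns the response being a decrease. The strata are cut on baseline SPPB, the same score from which the decrease is calculated. Regression to the mean then makes apparent falls more common in the healthy active stratum and less common in the frail one. If sleep disorders are more frequent in one stratum, this difference leaks into the sleep-disorder association unless the model accounts for it.

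**Working it through.** **1. Definitions side by side**

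| Stratum | Primary outcome (Outcomes) | Graded response (Statistical methods) | Same instrument? |
|---|---|---|---|
| Healthy active | SPPB below 9 at 12 months | Units of SPPB decrease | Yes |
| Physically frail sarcopenic | 400 m walk not completed in under 15 min | Units of SPPB decrease (no other response named) | No |

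**2. Share of expected events in the frail stratum**

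Inputs, all from Sample size: "overall sample size of 300 patients"; "assumption of the balanced numbers (1:1) of physically frail sarcopenic" and healthy active participants; "assumption of the unbalanced numbers (2:1) of individuals with and without sleep disorders at the baseline"; reference rates of 9% and 27%; overall risk ratio 1.55. The plan gives the exposure split and the risk ratio only overall. Applying them within each stratum is an assumption, and gives 100 exposed and 50 unexposed per stratum.

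- The plan's pooled rate is reproduced: 0.5 × 9% + 0.5 × 27% = 18%, as stated.
- Events per stratum = n(unexposed) × p0 + n(exposed) × p0 × RR.
- Frail: 50 × 0.27 + 100 × 0.27 × 1.55 = 13.5 + 41.85 = 55.35.
- Healthy active: 50 × 0.09 + 100 × 0.09 × 1.55 = 4.5 + 13.95 = 18.45.
- Frail share: 55.35 / 73.8 = 75%. Among the unexposed alone: 27 / (27 + 9) = 75%.

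**3. Sensitivity of the 75%**

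- Overall RR kept at 1.55 but differing by stratum. Exposed events total 200 × 0.18 × 1.55 = 55.8. With frail RR 1.0, the healthy active RR is (55.8 − 27) / 9 = 3.2 and the share is (13.5 + 27) / 73.8 = 55%. With healthy active RR 1.0, the frail RR is (55.8 − 9) / 27 = 1.73 and the share is (13.5 + 46.8) / 73.8 = 82%.
- RR 1.55 in both strata but uneven exposure. With 50 of the 200 exposed in the frail stratum, the share is 47.925 / (47.925 + 20.925) = 70%. With 150, it is 62.775 / (62.775 + 15.975) = 80%.

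In every variant the majority of events are walk failures.

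**4. Decrease as the response: illustration under no sleep effect**

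None of these inputs is in the document; all are assumed. Latent SPPB is normal with mean 8.5 and SD 2.4, the mean 12-month change is −0.3, and test-retest reliability is 0.7 to 0.9. Strata are formed on the observed baseline score. The model is a logistic regression for a fall of at least one point, which simplifies the planned ordinal model.

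| Sleep disorders, frail / healthy active | Covariates besides exposure | Odds ratio (true value 1) |
|---|---|---|
| 75% / 58% (about 2:1 overall) | None | 0.85 to 0.93 |
| 70% / 63% | None | About 0.95 |
| Equal in both strata | None | About 1.0 |
| 75% / 58% | Baseline SPPB, or stratum | About 1.0 |

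For scale, with 200 exposed and 100 unexposed and a fall in roughly half of participants, the standard error of the log odds ratio is about √(1/(200 × 0.25) + 1/(100 × 0.25)) = 0.245. Since ln 0.85 = −0.16, even the largest bias shown is about two-thirds of one standard error.

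**The case against.** The strongest reply is that the model is an addition. Inference rests on the test for two proportions applied to the stratum-specific outcome, and the article gives the ordinal model no confirmatory role and names its response openly. One scale across both strata is also a legitimate complement to a primary outcome that uses two instruments. This stands: the primary analysis is untouched, and modelling SPPB in both strata is acceptable if it is labelled as a separate outcome.

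It can also be said that the article does not state that the model covers everyone. That is correct; it is inferred from the absence of any restriction. If only the healthy active stratum was meant, the text needs to say so, and the frail stratum then has no graded analysis described. Either reading calls for a change of wording.

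A reader might infer that 75% of events go unscored by the ordinal model. The document does not support this. The 75% is the frail stratum's share of expected events. SPPB includes gait speed, chair stands and balance, so a participant who loses the ability to walk 400 m may well lose SPPB points too. The two patient examples show that discordance is possible, not how common it is.

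A reader might also infer that the planned model is biased towards showing no harm. That does not follow either. The bias needs unequal sleep-disorder prevalence and a model with neither baseline SPPB nor stratum. The model is called multivariable without a covariate list, which an article may leave to the analysis plan, and prevalence by stratum is not given. The Background does report that sleep anomalies associate with frailty, so imbalance is plausible, but its size is unknown.

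**Conclusion.** The concern holds as a mismatch between how the graded analysis is labelled and what it measures. As written, the ordinal SPPB model does not grade the primary outcome in the frail stratum. That stratum supplies about 75% of expected events under the plan's rates with a common risk ratio and exposure split, and 55% to 82% across the variants tried. How often SPPB decline and walk failure disagree cannot be determined from the document, and the primary two-proportion test is not affected.

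The regression-to-the-mean point is a conditional reason for care in specifying any SPPB model. It is not a demonstrated bias in this one. It is worth correcting before analysis because the change is nearly free and removes an avoidable ambiguity in interpretation.

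**What to change.** In Statistical methods, do one of the following:

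- describe the ordinal SPPB model as a separate supportive outcome analysed in both strata, not as the graded form of the primary outcome; or
- restrict it to the healthy active stratum, and grade the frail stratum on the 400 m walk, for example by completion time in ordered bands with non-completion as the worst category.

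In any SPPB model, use the 12-month score as the response in place of units of decrease, with baseline SPPB and, where both strata are included, frailty stratum as covariates. With the 12-month score as the ordinal response, the boundary between 8 and 9 that defines the healthy active outcome is one of the model's own thresholds.

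The cost is a few sentences and, under the second option, one more model. The 400 m walk and SPPB are already part of the assessment, so no new data are needed. The small downside of stratum-specific grading is two estimates instead of one.

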## Discussion

Using some of the most advanced diagnostic and digital health techniques, we will carry out a translational and multidimensional analysis of the changes induced by sleep disorders at the cerebral, muscular, metabolic, hormonal, cardiovascular, skeletal and body composition levels, in order to gain a deeper understanding of their pathophysiological role in the genesis of physical frailty and other relevant geriatric syndromes, as well as in the progression of these conditions towards dementia and mobility disability.

A 2-year prospective cohort design could be well-suited to elucidate temporal relationships between sleep disorders and changes in physical and functional status among older adults, as supported by longitudinal studies demonstrating associations between them and multimorbidity, frailty, and cognitive decline. The rationale for this approach includes the ability to capture incident outcomes and dynamic changes in sleep patterns, which is critical given the bidirectional nature of the relationship between sleep and aging.

It is well-known that sleep, during aging, undergoes architectural changes and that sleep disorders have in older people, traditionally affected by chronic diseases, different epidemiological characteristics than in younger ones. However, the classification of sleep disorders in older people has remained unchanged.

The profile of the subjects enrolled in our study, defined by specific inclusion and exclusion criteria, was specifically tailored to minimise the effect of comorbidities on the genesis of sleep disorders. This approach was used to ensure that those participants identified in our population sample were affected more likely by sleep disorders of primary rather than secondary origin.

Strengths of this design include also the ability to adjust for confounders and generalize findings to community-dwelling older adults. Limitations include potential selection bias, reliance on self-report for some sleep parameters, and challenges in disentangling causality due to complex interactions between sleep, aging, and comorbidities. Despite these limitations, prospective cohort studies demonstrated to be a good standard for investigating the impact of sleep disorders on aging trajectories [124–127].

Our methodological choices, incorporating both subjective and objective measures, as recently recommended by the American Heart Association [128], could comprehensively assess sleep health dimensions and minimize measurement bias. Furthermore, age-adapted analytic procedures we are planning to adopt, could account for interindividual differences and age-related changes in sleep physiology, as highlighted by recent methodological reviews [126].

Anticipated challenges include participant attrition, adherence to sleep monitoring protocols, and potential confounding from comorbidities, psychosocial factors, and medication use. On the other hand, regular follow-up, use of user-friendly wearable devices, robust statistical adjustment for covariates, and optimized sampling frequency represent countermeasures we are planning to involve and which allow to capture sleep variability, and not to miss key biological relationships as well [129, 130].

The project will allow to analyse sleep disorders, a public health problem, in the older population, where it is extremely relevant condition not fully addressed. In particular, reliance on subjective sleep assessment through questionnaires in cognitively frail individuals is known to introduce reporting bias, which can lead to under- or overestimation of sleep disturbances. On the other hand, objective sleep assessment through devices like actigraphs, sleep profilers, and cardio-respiratory monitors can mitigate this bias by providing quantifiable sleep parameters. Therefore, the inclusion of both types of measures, in research and clinical protocols, is known to represent the best opportunity to ensure robust and clinically meaningful assessment of sleep in vulnerable populations, as each provides distinct information: subjective measures reflect perceived sleep quality, while objective measures correlate more closely with sleep architecture. This approach will allow us to assess the sleep misperception, a relevant aspect of sleep health in this population [131–133].

By comparing the diagnostic capabilities of traditional techniques with the most innovative digital measurements in predicting the trajectories of physical, cognitive and quality-of-life functional decline, the expected results will highlight the importance of sleep as a fundamental determinant of ageing and healthspan. All these findings will allow the (digital health) improvement and personalisation of sleep disorders in a multidisciplinary assessment manner and to stimulate selective pharmacological treatment, and environmental hygiene measures (Fig. 6). These data will be translated in those individuals in whom routine therapeutic expedients have not provided substantial benefit.

